## Methods/design

### Study aims

This study will target provider- and patient-level barriers in order to improve utilization of lung screening and to achieve equity in screening rates by conducting a quasi-experimental study comparing a Multilevel Intervention to Usual Care. The Multilevel Intervention will perform inreach to educate patients about screening prior to their visit. At the same time, an EHR communication tool, similar to email, will send a reminder to primary care providers prior to scheduled visits with screening-eligible patients.

The *specific aims* of the trial are to (1) test the impact of the multilevel strategies on primary outcomes (provider-patient discussion, screening intentions, and knowledge) and secondary outcomes (screening referrals and screening completion rates) and (2) evaluate the implementation outcomes (adoption, feasibility, acceptability, fidelity).

The *hypotheses* are (1) participants in the Multilevel Clinics who receive the provider- and patient-level strategies will be significantly more likely to report having a screening discussion, intending to be screened, and having greater knowledge compared to the Comparison Clinic participants; (2) the multilevel, bundled strategies will increase screening referrals made by providers in the Multilevel Clinics; and (3) completion rates among the participants will be higher among the Multilevel Clinic participants compared to the Comparison Clinic participants. Finally, we will explore whether Health Disparities Framework factors (e.g., race, education, health literacy) moderate the outcomes (e.g., we expect that African Americans will have significantly greater knowledge in the Multilevel Clinics vs. the Comparison Clinics, whereas the strategies will have less of an impact among Whites).

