### Clinical setting and healthcare provider participants

MedStar Health, the largest not-for-profit health system in the Mid-Atlantic, includes more than 300 care locations including more than 60 ambulatory care centers, and primary and specialty care in academic medical centers and community-based clinics, 10 hospitals, and 33 urgent care clinics located in Baltimore, MD, Washington, DC, and Northern VA. This health system provides care to a diverse community which includes a large Black or African American population (44–73% in the participating clinics), and uninsured or underinsured individuals.

We will conduct the quasi-experimental study in partnership with four primary care, community-based ambulatory clinics within the MedStar Health system, matched on CT scanner on site (yes/no) and minority representation (> 40% Black or African American; Fig. 2). Clinic eligibility criteria include (1) clinic providers use the Message Center within MedConnect (Oracle Cerner); (2) > 400 patients who are 50–80 years old with a documented smoking history in the last 12 months; (3) > 40% African American patient population; and (4) a site champion who will serve as the primary point of contact for this study. The provider sample includes full- and part-time primary care providers at the participating clinics.

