### Patient recruitment and procedures

During the recruitment period, the research assistants will access the list of potentially eligible individuals from an EHR report that our team developed to identify patients with an upcoming visit who are 50–80 years old with an ever-smoking history. Due to the limitations of the EHR smoking history data, including a large number of missing data for the pack-years field (90% on average are missing pack-years), we are conservatively estimating 25% of those reached will be eligible for the study (Fig. 2). The report utilizes EHR appointment and clinical data and will be imported into the study’s REDCap database weekly by the study team. Our team will invite patients to participate in the study through a mailed invitation letter, email, and the myMedStar patient portal, followed by phone calls (up to 3 attempts). During this call, the research staff member will describe the study, determine eligibility, obtain verbal consent, and complete the baseline assessment. We expect to enroll *n* = 184 in the Multilevel Clinics and *n* = 184 in the Comparison Clinics (total *N* = 368).

Following baseline (T0), Multilevel Clinic participants will receive the phone-based inreach and education within 1 week to 3 days prior to the visit. The comparison clinics will not receive the bundled strategies, but eligible participants will be enrolled and followed to measure the outcomes. All patient participants will receive up to $50 in total for their participation.

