### Measures

We will use mixed-methods and multilevel assessments (Table 1). At the *patient-level*, participants will be assessed at baseline and 1-week post-visit to measure the primary outcomes: provider-patient discussion (“Did you have a discussion with your doctor about lung screening?”), screening intentions (“Do you plan to have a CT scan to check for lung cancer in the next 6 months?”), and knowledge using 11 true/false items from the literature [47]. We will administer the Questionnaire on the Quality of Physician–Patient Interaction scale to measure patient-reported provider-patient communication [48]. The Lung Screening Health Beliefs Scale will measure perceived risk, self-efficacy, benefits, and barriers [49]. The Consumer Health Activation Index will be administered to measure patient activation [35]. We will evaluate potential moderators including race (non-Hispanic African American vs. non-Hispanic White vs. other), smoking status (current vs. former), and health literacy (“How often do you find numbers, figures, or graphs to be useful in making a health-related decision?”) [50].

**Table 1 Tab1:** Complete measures

		**T0**	**T1**	**T2**
		**Baseline**	**1 week**	**6 months**
***Patient-level variables***	*Primary outcomes*: Provider-patient discussion, lung screening intentions, screening knowledge	**X**	**X**	
	*Secondary outcomes*: Lung screening referrals, completion rates (EHR)	**X**		**X**
	*Moderators*: Race, smoking status, health literacy	**X**		
	*Intervention targets*: Physician–patient communication, perceived risk, self-efficacy, benefits/barriers, patient activation, attended visit/visit type	**X**	**X**	
	*Covariates*: Demographics, social determinants of health, tobacco behaviors, cancer screening history, psychological variables (e.g., stigma, medical mistrust)	**X**		
***Provider-level variables***	Demographics	**X**		
	Lung screening practices	**X**		**X**
	Lung screening attitudes	**X**		**X**
	Intervention acceptability, usability, intervention, effectiveness			**X**
***Implementation variables***	Reach: % of patients offered trial enrollment and the % enrolled out of the number of eligible patients who had a visit during the recruitment period	**Pre-post implementation**		
	Effectiveness: screening referrals and screening completion rates			
	Adoption: % of messages opened by the receiving provider; fidelity of the patient component			
	Implementation: feasibility, acceptability			

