### Sample size and power

All power calculations were performed for the primary outcomes (provider-patient discussion, screening intentions, and knowledge), using intention-to-treat principles, and a significance level of 0.05. We will have 83% power to detect a difference of 12% for the provider-patient screening discussion, a difference of 15% for likely screening intention, and an effect size of 0.33 for the screening knowledge score. For the moderation analyses, we will have > 80% power to detect an effect size of 0.50 with equal subgroups (e.g., Black vs White, high vs. low literacy levels).

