### Statistical analysis plan

We will examine the distributions of all variables to describe the characteristics of the study population. We will conduct analyses using *t*-tests, *χ*^2^ tests, and Pearson or Spearman correlation coefficients to assess the bivariate associations between the baseline characteristics and the outcome variables. Bivariate analyses will also be conducted to assess the associations between the study arm and baseline characteristics. Owing to any significant differences detected at the 0.05 level, the variables associated with both the study arm and the outcome of interest will be entered as covariates in subsequent analyses. To test the overall difference between the study arms on the primary outcomes, we will conduct logistic regression models (for provider-patient discussion — yes/no, screening intentions — likely/unlikely) and a linear regression model (for the screening knowledge score). Logistic regression analyses will also be conducted on the secondary screening outcomes (lung screening referral — yes/no, lung screening completion — yes/no). This study will explore potential moderators (e.g., race, health literacy, smoking status). That will be done by evaluating the presence of interactions between the moderators and study arm, one at a time, after adding them to the regression models described above. In sensitivity analyses, we will evaluate the robustness of our findings by using versions of the above models with generalized estimating equations (GEE). These models will use the sites as clusters, and assume an exchangeable working correlation structure.

For the qualitative analysis, we will use a deductive thematic analysis based on a priori PRISM constructs, with additional codes added as needed. Initial codes will be generated by two coders and each of the coders will review two transcripts for each sub-population (i.e., patient and provider) to reach a consensus on the coding framework and application of codes prior to splitting up the remaining transcripts.

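### Choosing covariates by two bivariate 0.05 tests can drop weak-to-moderate confounders and leave residual bias in this non-randomised comparison

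*Protocol article*

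**What the plan says.** The Study aims section describes a "quasi-experimental study comparing a Multilevel Intervention to Usual Care". The setting is "four primary care, community-based ambulatory clinics within the MedStar Health system", and the clinics are "matched on CT scanner on site (yes/no) and minority representation". Enrolment is "184 in the Multilevel Clinics" and the same number in the Comparison Clinics.

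The Statistical analysis plan first tests baseline characteristics against the outcomes and against study arm, each time bivariately. The entry rule that follows is that "the variables associated with both the study arm and the outcome of interest will be entered as covariates in subsequent analyses". Its threshold is set by the opening words of the same sentence: "Owing to any significant differences detected at the 0.05 level". The resulting models cover three primary outcomes (discussion, intention, knowledge) and two secondary ones (referral, completion).

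Table 1 in the Measures section lists covariates collected at T0: "Demographics, social determinants of health, tobacco behaviors, cancer screening history, psychological variables", with stigma and medical mistrust as examples of the last group. It also marks the primary outcomes as measured at T0. Nothing in the analysis section commits to adjusting for any of these. The GEE sensitivity analysis refits the same models with sites as clusters and names no other covariate set.

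**The concern.** The bias that a confounder causes depends on its imbalance between arms multiplied by its association with the outcome. Two p-values measure something else: whether each of those quantities is large relative to its standard error at this sample size. A variable with a modest imbalance and a modest outcome association can fail either test and still contribute bias, and several such variables add up if they act in the same direction.

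There are three further consequences:
- Variables that predict the outcome but are balanced between arms are left out, which gives up precision.
- Selection happens after outcomes are seen, and the model-based p-value and interval take no account of it.
- The covariate set can differ from outcome to outcome, so the five arm effects need not be adjusted for the same things.

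Race shows the practical effect. It is a hypothesised moderator, yet it enters the overall arm comparison only if it passes both tests.

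**Working it through.** **Inputs from the article.** 184 per arm (368 in all), significance level 0.05, knowledge target 0.33 SD, and the two-test rule.

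**Assumptions, because the article gives no confounder strengths.** Independent binary confounders, no true arm effect, residual SD of 1 for the knowledge score, no clinic effects, complete data. The first cases have every confounder acting in the same direction.

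**The plan's own figure.** The article gives no figure for covariate selection. Its nearest figure is 83% power for 0.33 SD. At 184 per arm, Φ(0.33 × √92 − 1.96) = 88.6%. With 15% attrition (an assumption; about 156 per arm) it is 83.0%. Attrition is not stated, so the 83% is neither confirmed nor refuted, and this point does not rest on it.

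**Step 1: chance that a true confounder is kept.** For K confounders, arm difference d and effect b:
- Arm test: z = d / √{[p0(1−p0) + p1(1−p1)]/184}. For 45% v 55%: 0.10/√(0.495/184) = 1.93, so the chance of passing is Φ(1.93 − 1.96) = 0.49.
- Outcome test (arms pooled): the difference in mean outcome is b + d × (K−1) × b × d, because the other confounders also differ by arm. For five: 0.25 + 0.10 × 4 × 0.025 = 0.26. The outcome SD is √(1 + K b²/4) = 1.038, and z = 0.26/(2 × 1.038/√368) = 2.40, so the chance of passing is Φ(0.44) = 0.67.
- Both: 0.49 × 0.67 = 0.33.

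| Assumed case | Arm test | Outcome test | Product | Kept in simulation |
|---|---|---|---|---|
| Five, 45% v 55%, 0.25 SD | 0.49 | 0.67 | 0.33 | about 34% |
| Eight, 46% v 54%, 0.20 SD | 0.34 | 0.49 | 0.16 | about 18% |
| Five, 40% v 60%, 0.25 SD | 0.97 | 0.76 | 0.74 | about 75% |

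**Step 2: bias and type I error.** Unadjusted bias is K × d × b: 5 × 0.10 × 0.25 = 0.125; 8 × 0.08 × 0.20 = 0.128; 5 × 0.20 × 0.25 = 0.25 SD. The remaining columns are simulated.

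| Assumed case | Unadjusted bias; type I | Two-test rule | Complete fixed set |
|---|---|---|---|
| Five, 45% v 55% | 0.12 SD; 21% | 0.05 SD; 8% | 0; 5% |
| Eight, 46% v 54% | 0.13 SD; 21% | 0.07 SD; 10% | 0; 5% |
| Five, 40% v 60% | 0.25 SD; 64% | 0.03 SD; 5–6% | 0; 5% |

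Against the 0.33 SD target, 0.05 is 15% and 0.07 is 21%. The bias left is smaller than the share of variables dropped would suggest (0.66 × 0.125 = 0.08 in the first case), because the dropped variables tend to be those with the smaller observed imbalance or association.

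**Step 3: direction.** With the sign of each confounder drawn at random, type I error under the rule is about 5% in both the five-confounder (45% v 55%) and the eight-confounder case.

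**Step 4: binary outcome.** Assume continuous confounders and a 10% base rate. Eight confounders (0.2 SD imbalance, odds ratio 1.5 per SD) leave a log odds ratio bias of 0.23 and type I error of 12%, against 0.56 and 53% unadjusted and 0 and 6% with the complete set. Confounding can also hide an effect. With four confounders working against a true log odds ratio of 0.93 (0.3 SD imbalance, odds ratio 1.3), the rule estimates 0.75 with 67% power, against 0.95 and 83% with the complete set.

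**Step 5: precision.** If a fixed set explained 10–20% of knowledge variance (an assumption), power at 0.33 SD would be Φ(0.33 × √(92/(1−R²)) − 1.96) = 91.6–94.3%, against 88.6% without it, for independent patients.

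**The case against.** The strongest reply is that the rule does much of its job. In the first two cases it removes about 60% (1 − 0.05/0.125) and 45% (1 − 0.07/0.128) of the unadjusted bias, and at 40% v 60% about 88% (1 − 0.03/0.25). It works best where confounding is largest. This stands. A reader might infer that most real confounders are dropped, but the article gives no strengths from which to say so. For continuous confounders with an imbalance of 0.3 SD or more and an outcome correlation of 0.15 or more, 68–100% are kept.

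A second reply is that the type I inflation needs confounders aligned in one direction. This also stands for the average over trials, although any single trial keeps whatever residual bias its own confounders produce.

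Third, the fixed-set result of 5% assumes that the set contains every confounder. With two of the five left out, the bias is 2 × 0.10 × 0.25 = 0.05 SD, the same as under the rule. At 40% v 60% it is 2 × 0.20 × 0.25 = 0.10 SD, worse than the rule's 0.03. So the benefit shown is an upper bound and depends on a well-chosen set.

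Fourth, a reader might infer that adjustment is the only protection against differences in patient mix. It is not: clinic matching and common eligibility criteria (age, pack-years, non-adherence, a scheduled visit) also limit them. These are partial. The participating clinics still range from 44% to 73% Black or African American.

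Finally, the Discussion concedes limited causal inference. That concession is fair, but it is no reason to keep a selection rule that weakens the adjustment.

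**Conclusion.** The point holds as a weakness in a stated rule, not as proof that the result will be biased. The article fixes a data-driven entry rule, forces no covariate in, and offers no sensitivity analysis with a different set. Under modest, same-direction confounding, the rule would leave roughly 0.05–0.07 SD of bias in the knowledge score and type I error of about 8–10%. With larger imbalance the bias falls to about 0.03 SD, and with random directions type I error is close to 5%.

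These figures rest on assumed confounder strengths, independent patients and no clinic effects, so they are not the trial's actual error rates. The stronger reading, that the arm effect necessarily stays biased, is not supported: with few or strong confounders the residual is near zero. The loss of balanced prognostic variables and the possibility of a different set for each outcome follow from the rule itself and need no assumed strengths. The change is worth making because it is cheap and the data are already planned.

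**What to change.** Replace the two-test rule with one covariate set, fixed before outcome data are seen, used in the models for all five outcomes and kept whatever its p-values. Draw it from the T0 measures in Table 1: for example age, sex, race, education, smoking status, screening history, the main social-determinant measure, and stigma or medical mistrust. Add the baseline value of the outcome where it is meaningful, such as T0 knowledge and T0 intention. Use baseline comparisons between arms descriptively only. If screening completions are few, carry the same set through a propensity score or a penalised logistic model.

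The cost is one paragraph of analysis wording and a few more model parameters; no new data are needed. The change does not remove unmeasured confounding, or clinic-level confounding with four clinics, and its benefit depends on how complete the fixed set is. The article's caution about causal claims should stay.

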**Methods:**

Guided by the Health Disparities Research Framework and the Practical, Robust Implementation and Sustainability Model, we will conduct a quasi-experimental study with four primary care clinics within a large health system (MedStar Health). Individuals eligible for lung cancer screening, defined as 50–80 years old, ≥ 20 pack-years, currently smoking, or quit < 15 years, no history of lung cancer, who have an appointment scheduled with their provider, and who are non-adherent to screening will be identified via the EHR, contacted, and enrolled (*N* = 184 for implementation clinics, *N* = 184 for comparison clinics; total *N* = 368). Provider participants will include those practicing at the partner clinics (*N* = 26). To increase provider-prompted discussions about lung screening, an electronic health record (EHR) clinician reminder will be sent to providers prior to scheduled visits with the screening-eligible participants. To increase patient-level knowledge and patient activation about screening, an inreach specialist will conduct a pre-visit phone-based educational session with participants. Patient participants will be assessed at baseline and 1-week post-visit to measure provider-patient discussion, screening intentions, and knowledge. Screening referrals and screening completion rates will be assessed via the EHR at 6 months. We will use mixed methods and multilevel assessments of patients and providers to evaluate the implementation outcomes (adoption, feasibility, acceptability, and fidelity).

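### The arm effect is tested with patient-level regressions that ignore assignment by clinic (two clinics per arm), and the four-site GEE, as described, cannot show that the result is robust

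*Protocol article*

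**What the plan says.** The study is run in "four primary care, community-based ambulatory clinics within the MedStar Health system" (Clinical setting and healthcare provider participants). Its aim is described as "conducting a quasi-experimental study comparing a Multilevel Intervention to Usual Care" (Study aims).

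Treatment goes by clinic: "The comparison clinics will not receive the bundled strategies, but eligible participants will be enrolled and followed to measure the outcomes" (Patient recruitment and procedures). Both arms are called clinics in the plural and there are four in all, so the split must be two and two. The same section expects 184 patients in each arm, 368 in total. The reminder goes to primary care providers, and the Abstract gives 26 provider participants.

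For the arm comparison, the Statistical analysis plan section says "To test the overall difference between the study arms on the primary outcomes, we will conduct logistic regression models" for discussion and intention, with a linear regression for the knowledge score. Logistic regression is also used for the two secondary outcomes, referral and completion. No clinic or provider term and no clustered variance is mentioned. Clustering enters only in a sensitivity analysis by GEE: "These models will use the sites as clusters, and assume an exchangeable working correlation structure". Sample size and power gives a 0.05 significance level and 83% power, with no ICC or design effect.

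**The concern.** Patients of one clinic share providers, workflow and local screening practice. Discussion and referral are largely provider behaviours, so some similarity within clinics is to be expected. The clinics are matched only on having a CT scanner on site and on minority representation. Any other difference between the two pairs of clinics goes straight into the arm contrast. A patient-level regression measures that contrast against patient-to-patient variation alone, so its standard error is too small.

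The stated check on robustness uses four clusters. If its variance is also too small, it will tend to confirm a false positive. An ordinary difference between clinics could then be reported as an effect of the multilevel strategy on any of the three primary or two secondary outcomes, and could be carried into the larger trial that the Discussion foresees.

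**Working it through.** **Inputs.** From the article: 4 clinics, 184 patients per arm, significance level 0.05, knowledge effect size 0.33. Assumed: 2 clinics per arm with 92 patients each (184 / 2), a two-sided test, and clinic ICCs from 0 to 0.05.

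**1. The stated power.** With independent patients, power for knowledge is Φ(0.33 × √(n/2) − 1.96). At n = 184 this is Φ(3.165 − 1.96) = 88.6%. The stated 83% appears at n = 156 per arm: Φ(2.915 − 1.96) = 83.0%, which would correspond to about 15% attrition, a figure the article does not give. For a 15-point difference in intention, 184 per arm gives 82–83% at control rates of about 35–50%. For a 12-point difference in discussion it gives about 83% at a control rate between 12% (85.3%) and 15% (80.9%). The stated power can therefore be reached without any design effect, but only with inputs that are not reported.

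**2. Type I error of the planned primary models.** With m patients per clinic the variance of the contrast is inflated by DE = 1 + (m − 1) × ICC. The true error rate of the nominal 5% test is then about 2 × [1 − Φ(1.96 / √DE)].

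- ICC 0.005: DE = 1 + 91 × 0.005 = 1.46, error rate 10.4%
- ICC 0.01: DE = 1.91, error rate 15.6%
- ICC 0.02: DE = 2.82, error rate 24.3%
- ICC 0.05: DE = 5.55, error rate 40.5%

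**3. Type I error of the four-site GEE.** Take the balanced, unadjusted, continuous case. Let D be the difference between arm means and SS the sum, over both arms, of squared deviations of clinic means from their arm mean. The uncorrected sandwich variance of D is SS/4. The unbiased estimate is SS/2, on 2 degrees of freedom. The sandwich z-statistic is therefore √2 times a t-statistic on 2 df, and it rejects when |t| > 1.96 / √2 = 1.386. For 2 df, P(|t| > x) = 1 − x / √(2 + x²), so the error rate is 1 − 1.386 / √3.921 = 30%. The ICC cancels, so this holds even with no clustering. Correcting the variance but keeping the normal reference gives 1 − 1.96 / √5.842 = 19%. Correcting the variance and using t on 2 df (critical value 4.303) gives 5%, and is then the same test as a t-test on the four clinic means.

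**4. Simulation** (no true effect, 4 × 92 patients, continuous outcome, 200,000 replicates per ICC):

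| Clinic ICC (assumed) | Planned primary model | Four-site GEE, sandwich and z | Clinic means, t on 2 df |
|---|---|---|---|
| 0 | 4.9% | 30% | 5.0% |
| 0.005 | 10.5% | 30% | 5.0% |
| 0.01 | 15.6% | 30% | 5.0% |
| 0.02 | 24.6% | 30% | 5.0% |
| 0.05 | 41.0% | 30% | 5.1% |

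Binary outcomes at null rates of 15–40% behave alike: the logistic model rejects about 10%, 15–16%, 24–25% and 40–41% at ICC 0.005, 0.01, 0.02 and 0.05, and the GEE about 30%.

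**5. Value of the GEE as a check.** Among data sets in which the primary model is falsely significant, the uncorrected GEE is significant too in about 87%, 81%, 72–73% and 59–60% at those four ICCs.

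**6. Price of a valid test.** For d = 0.33, the t-test on clinic means has power of about 42%, 32%, 26%, 20% and 13% at ICC 0, 0.005, 0.01, 0.02 and 0.05. The half-width of its 95% interval is about 4.303 × √(ICC + (1 − ICC)/92). That is 0.45 SD at ICC 0 and 0.62 SD at ICC 0.01.

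**The case against.** Four points on the other side deserve weight.

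- A reader might infer that no planned test of the arm effect holds 5%. The article does not support that: it gives no ICC, and at an ICC of zero the primary models hold their level. The 10–41% is a conditional range, and 92 per clinic is an even-split assumption.
- A reader might also infer that a four-site GEE is invalid in itself. The article names the clusters and the working correlation but neither the variance estimator nor the reference distribution, which a fuller analysis plan may fix. With a small-sample correction and t on 2 df the GEE holds 5%. The 30% belongs only to the uncorrected default. Even a corrected GEE would remain a sensitivity analysis while the primary tests stayed unclustered.
- Clustering by provider might look like the natural remedy, with 26 providers instead of four clinics. It leaves clinic-level error in place. A provider-level test (26 providers, 14 patients each, provider ICC 0.05) still rejects about 10–11%, 15% and 25–26% at clinic ICC 0.01, 0.02 and 0.05.
- The Discussion already calls the results preliminary, says that the design limits causal conclusions, and defers to a cluster randomized trial. Clinic-level orders and completion rates are also collected for 12 months before and after the study, which informs on existing clinic differences in the secondary outcomes. This softens the interpretation but does not repair the p-values, and Study aims still words its first hypothesis in terms of statistical significance.

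**Conclusion.** The concern stands as an analysis that the article itself fixes, not as detail left to another document. The primary and secondary tests treat patients as independent although assignment is by clinic with two clinics per arm. Their type I error is about 10%, 16%, 24% and 41% at assumed clinic ICCs of 0.005, 0.01, 0.02 and 0.05, and 5% only if the ICC is essentially zero. The sensitivity GEE as described cannot demonstrate robustness: under the usual sandwich variance and normal reference it rejects about 30% of the time whatever the ICC. These figures assume 92 patients per clinic, a two-sided test and no true effect. Even with a valid test, two non-randomized clinics per arm do not allow the clinic effect to be separated from the strategy effect.

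**What to change.** 1. Base inference on the arm effect on a clinic-level analysis with its degrees of freedom stated. Either use covariate-adjusted clinic summaries compared by t on 2 df, or use the four-site GEE with a small-sample variance correction and a t reference on 2 df. The two are equivalent in the balanced, unadjusted case. Either replaces an uncorrected four-cluster GEE.
2. Report the patient-level logistic and linear regressions as estimates with confidence intervals, labelled as not accounting for between-clinic variation, and reword the first hypothesis so that it does not read as a confirmatory significance claim.
3. State among the limitations that, with two non-randomized clinics per arm, clinic and strategy effects cannot be separated.
4. A provider-clustered model may be added as supportive only. Reminders identify the provider in the Multilevel Clinics alone; for comparison patients the provider would have to come from another source, such as appointment data.

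Only protocol and analysis wording changes. The cost is statistical: very wide intervals, and power for the stated knowledge effect of about 42% at best, falling to 13% at a clinic ICC of 0.05.
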